### 9.3 Study cohorts/data sets to be evaluated

For the statistical analysis the included subjects will be divided up into the following datasets:

Safety set (SAS): This is the subset of subjects who received at least one dose of study vaccine and for whom any safety data are available.

The final safety analysis will be performed on this population.

Full-analysis set (FAS): This is the subset of subjects who had received at least one dose of study vaccine and for whom any data are available.

Modified Full Analysis Set (MFAS):

This set is defined to consist of all enrolled vaccinia-naïve healthy (Group 1) and at least 300 atopic dermatitis (Group 2) subjects.

- who have been enrolled as vaccinia-naïve based on the verbal confirmation of the volunteer not to have had a smallpox vaccination in the past and on examination of both arms for absence of a typical smallpox vaccination scar.
- who had received both doses of study vaccine and completed all study visits including Visit 4 and
- for whom safety data are available.

Per Protocol (PP) set: This is the subset of subjects who adhere to all protocol conditions, however, not relevant protocol violators can be included into this dataset.

The decision whether a protocol deviation is relevant or not for the classification of subjects to subsets should be made case-by case in a blind review meeting.

The primary population dataset for humoral immunogenicity analysis (ELISA and PRNT) will be the PP set. All confirmatory testing is based on this population. For further descriptive purposes, the same statistical procedures will be applied to the FA dataset.

ELISPOT Analysis Set (EAS):

This set is defined as the alternative PPS for the ELISPOT data analysis. It consists of all subjects with

- a complete ELISPOT data set (Visits 1, 2 and 4 available)
- the administration of both study vaccinations
- without any relevant major protocol violations for this data set.

ELISPOT data analysis will be descriptive and performed on both the EAS and the FAS.

Since two different vaccine lots will be used during the conduct of the study, a stratified subgroup analysis comparing subjects vaccinated either with vaccine lot 0170505 or vaccine lot 0040707 will be performed.

Any subject not included in the Full Analysis Set (FAS) will be considered a drop-out.

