### 5.4 Individual withdrawal criteria during the study

Subjects may withdraw or be removed from the study for any of the reasons cited below:

- An adverse event occurs that, in the opinion of the Investigator, makes it unsafe for the subject to continue the study. In this case, the appropriate measures will be taken.
- Subject's request to withdraw.

- Subject unwilling or unable to comply with study requirements.
- Clinical need for concomitant or ancillary therapy not permitted in the study.
- Unrelated intercurrent illness that, in the judgment of the Principal Investigator, will affect assessment of clinical status to a significant degree.

The following criteria should be checked at any visit after enrollment into the study. If any become applicable during the study, the subject may be withdrawn:

Use of any investigational or non-registered drug or vaccine other than the study vaccine(s).  
Administration of a licensed vaccine not foreseen by the study protocol during the study period.  
Start of chronic administration (defined as more than 14 days) of systemic immuno-suppressants during the study period.  
Administration of immunoglobulins and/or any blood products during the study period.

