## 5.6 Contraindications and precautions for further study vaccinations

### Absolute contra-indications:

The following events constitute absolute contra-indications to further administration of the study vaccine; if any of these occur during the study, the subject must not receive additional doses of vaccine, but may continue other study procedures at the discretion of the Investigator. The subject must be followed until resolution of the event, as with any adverse event:

- Anaphylactic reaction following the administration of vaccine(s).
- Pregnancy.

Subjects who become pregnant during the study period (up to and including one month [minimum 28 days] after receiving the last vaccine dose) must not receive additional doses of vaccine but may continue other study procedures at the discretion of the Investigator.

Subjects should be instructed to notify the Investigator if it is determined after completion of the study that they became pregnant either during the study or within one month (minimum 28 days) after receiving the last vaccine dose. Pregnancy must be reported to BN on a Pregnancy Form within 24 hours of the Investigator's becoming aware of the event.

A pregnancy should be followed to term, any premature terminations reported, and the health status of the mother and child including date of delivery and the child's gender and weight should be reported to Bavarian Nordic after delivery.

Temporary deferral of vaccination:

The following adverse event constitutes a contra-indication to administration of the study vaccine at that point in time; if this adverse event occurs at the time scheduled for vaccination, the subject may be vaccinated at a later date or withdrawn at the discretion of the Investigator. The subject must be followed until resolution of the event, as with any adverse event:

- Acute disease at the time of vaccination. (Acute disease is defined as the presence of a moderate or severe illness with or without fever. The vaccine can be administered to persons with a minor illness such as diarrhea, mild upper respiratory infection with or without low-grade febrile illness, i.e., oral temperature  $\leq 100.4^{\circ}\text{F}$  ( $\leq 38.0^{\circ}\text{C}$ ).

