## 9.4 Statistical analysis

Once all subjects have completed the half-year follow-up (Visit F-U) and after any necessary settlement of queries etc. in the CRFs, data from all patients and visits will be locked. A full

analysis of the data available will be performed and a final clinical study report prepared. Results of the PRNT assay will be presented in an addendum to the clinical study report. For preparation of safety data as part of a potential Emergency Use Authorization (EUA) data package, a safety analysis will be performed on the population (MFAS) described in section 9.3 ('Study cohorts/data sets to be evaluated').

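### The safety tables for the potential EUA package use a two-dose completer set (MFAS), which omits vaccinated subjects whose reaction prevents dose 2 or a visit through Visit 4

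*Protocol*

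**What the plan says.** Section 9.3 of the protocol defines two populations that bear on safety.

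- **SAS:** "This is the subset of subjects who received at least one dose of study vaccine and for whom any safety data are available". The section then adds: "The final safety analysis will be performed on this population".
- **MFAS:** "This set is defined to consist of all enrolled vaccinia-naïve healthy (Group 1) and at least 300 atopic dermatitis (Group 2) subjects". Its members must also be subjects "who had received both doses of study vaccine and completed all study visits including Visit 4 and" for whom safety data are available.

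Section 9.4 assigns the second of these to the EUA work: "a safety analysis will be performed on the population (MFAS) described in section 9.3".

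Two other sections determine who can reach dose 2 and Visit 4. Section 5.6 lists an anaphylactic reaction among the absolute contra-indications and states that "if any of these occur during the study, the subject must not receive additional doses of vaccine, but may continue other study procedures". Section 5.4 permits withdrawal when "An adverse event occurs that, in the opinion of the Investigator, makes it unsafe for the subject to continue the study". Section 5.1 also allows participation to be halted for a single subject after a possibly related serious event, or after an unexpected systemic reaction or laboratory toxicity of grade 3 or higher.

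Appendix IV (16.4.4) makes the frequency of reactions in 300 AD subjects the primary objective of the extension. It states that this number detects a 1-in-100 reaction with 95% confidence. Section 16.4.1 ties the figure of 300 to the data expected in support of an EUA.

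**The concern.** Membership of the MFAS depends on what happened after vaccination, and part of what happens after vaccination is the outcome being measured. A subject with a severe reaction to dose 1 may attend every later visit, as section 5.6 allows, and still be outside the set for want of a second dose. A subject who misses Visit 4 because of a reaction to dose 2 is outside it too. The reactions most likely to be lost are those serious enough to change the subject's course in the trial.

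At stake are the EUA tables: the reaction rates shown there, and the chance that an uncommon reaction in AD subjects appears in them at all. The statement about detecting a 1-in-100 reaction carries over to the MFAS only if no reactor is excluded from it.

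**Working it through.** **Inputs from the protocol**

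- Planned AD subjects: 130 + 200 = 330 (sections 3.2.4 and 4.1; table in Appendix V).
- Minimum AD count in the MFAS: 300 (section 9.3).
- Design target: at least one event at an incidence of 1:100, with 95% probability (section 16.4.4).

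**Input not in the protocol**

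- *f*, the share of reactors who miss dose 2 or a visit through Visit 4 because of the reaction. It is varied from 0 to 1 as an assumption. Losses for other reasons are taken to be unrelated to the reaction.

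**Step 1: the plan's own figure.** The chance of at least one event is 1 − (1 − p)^N. With p = 0.01 the smallest N giving 95% is 299, against 298 in the table in section 16.4.4, a difference of rounding. At N = 300 the chance is 1 − 0.99^300 = 95.1%. The plan's figure is reproduced.

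**Step 2: the rate seen in the MFAS.** If p is the true rate among vaccinated subjects and a share f of reactors is removed, the rate among those left is p(1 − f) / (1 − pf). This equals p at f = 0 and is below p for any f above 0. For f = 0.5 it is 0.005 / 0.995 = 0.503%.

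**Step 3: the chance of seeing at least one reaction.** With 300 MFAS subjects it is 1 − (1 − MFAS rate)^300. The last column instead takes 330 vaccinated subjects and removes reactors only: 1 − (1 − p(1 − f))^330.

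| f (assumed) | MFAS rate | Chance, MFAS of 300 | Chance, 330 vaccinated, only reactors lost |
|---|---|---|---|
| 0 | 1.000% | 95.1% | 96.4% |
| 0.10 | 0.901% | 93.4% | 94.9% |
| 0.25 | 0.752% | 89.6% | 91.7% |
| 0.50 | 0.503% | 77.9% | 80.9% |
| 1 | 0% | 0% | 0% |

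**Step 4: the SAS.** If all 330 planned AD subjects are vaccinated and give any safety data, the chance is 1 − 0.99^330 = 96.4%, whatever f is. The step from 95.1% to 96.4% at f = 0 comes only from the larger number of subjects. The fall down each column is the effect of excluding reactors.

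**Step 5: room for exclusions.** The MFAS can stand at its stated minimum with 330 − 300 = 30 AD subjects missing, or 30/330 = 9.1%. This is slack in the definition, not expected attrition.

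**The case against.** The strongest reply is that the reactions are not lost from the trial's reporting. The final safety analysis is on the SAS, which keeps every vaccinated subject with any safety data. The rationale for Amendment 6 places the EUA safety report inside the final study report, so both sets of results will be in one document. Section 9.4.3 has each serious event described individually, and events of special interest listed and tabulated for the whole study. Section 9.4.4 has all case report form data listed. A dose-1 anaphylactic reaction would be visible.

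This stands, and it confines the point to the MFAS-based tables. A reader might infer that the reported safety profile as a whole is biased; the documents do not support that. The reply does not cure the tables themselves. Section 9.4 names only the MFAS for the EUA safety data, and nothing calls for the SAS results beside it or for a list of those it omits. Non-serious grade 3 reactions outside the special-interest definition would appear in general listings but have no individual narrative.

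A second reply is that the error need not always be favourable. Sections 9.4.3 and following summarise solicited events per patient as well as per vaccination, and two-dose subjects have two chances to report. For reactions that do not stop vaccination, the per-patient MFAS rate could exceed the SAS rate. This also stands, so the direction is claimed only for reactions that prevent dose 2 or a visit through Visit 4.

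A reader might also take the drop-out rule ("Any subject not included in the Full Analysis Set (FAS) will be considered a drop-out") as part of the same bias. It is true that a subject stopped after dose 1 is in the FAS and so is not a drop-out. But the definition enters no numerator or denominator of a safety rate. Nor does the replacement of unvaccinated subjects in section 5.5 force the drop-out count to zero: those subjects are outside the FAS and therefore count as drop-outs under section 9.3, replaced or not. The definition is awkward, but it is a separate and minor matter.

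**Conclusion.** The point holds for the EUA safety tables only. Sections 9.3 and 9.4 together condition a safety population on completing vaccination and visits, while sections 5.1, 5.4 and 5.6 let reactions end vaccination or participation. For such reactions the MFAS rate can only be too low, on the assumption that other losses are unrelated to the reaction.

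The size cannot be fixed from the protocol, because it does not say how many subjects a reaction would stop. The effect is nil if there are none. If a quarter of reactors were stopped, a true 1-in-100 reaction would have an 89.6% chance of appearing among 300 MFAS subjects; if half were, 77.9%. Both shares are assumptions. The SAS on all 330 planned AD subjects gives 96.4%.

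The primary endpoint and the SAS-based final safety analysis are untouched. This should be fixed, but it is not a defect that invalidates the plan.

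**What to change.** In section 9.4, name the SAS as the population for the EUA safety analysis and keep the MFAS tables as supportive. Add a listing of every vaccinated subject excluded from the MFAS, with the reason and all recorded adverse events, so that a reader can move from one denominator to the other.

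In section 9.3, it would help to state the MFAS as a membership rule. As worded, it combines all enrolled healthy subjects with a two-dose, Visit 4 requirement, and gives a target number for the AD group.

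The cost is wording, a change of population flag and one listing. The SAS is already defined and used for the final safety analysis, and the date and reason of discontinuation are already collected under section 5.5. The one downside is that the EUA rates may look slightly less favourable.

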## 2. Objectives

### The primary objective of the trial is:

- To assess the humoral immune responses (measured by ELISA) induced to MVA-BN® (IMVAMUNE®) in subjects with diagnosed atopic dermatitis compared to healthy subjects.

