### 3. Study design

#### 3.1 Experimental design

This study is an open-label, controlled, phase II clinical trial to evaluate immunogenicity and safety of MVA-BN® (IMVAMUNE®) smallpox vaccine in 18-40 year old subjects with diagnosed atopic dermatitis.

The following two subject groups are compared:

Group 1: Healthy, vaccinia naïve subjects without atopic disease

Group 2: Vaccinia naïve subjects with diagnosed atopic dermatitis. “Diagnosed” atopic dermatitis includes subjects with either history of or subjects with currently active (defined as SCORAD  $\leq$  30, Kunz et al., 1997) atopic dermatitis.

[figure not shown]

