## 6.6 Concomitant medication

All concomitant medication must be recorded in the CRF with the reason for administration, the dosage regimen, and the onset and end of treatment.

For subjects with active AD, the use of calcineurin inhibitors during the study defined as  $\leq 10$  grams/week of tacrolimus (0.1% ointment) or pimecrolimus (1% cream) only on small areas of the face (defined as  $\leq 25\%$  of facial surface area) is allowed. The use of calcineurin inhibitors on body areas other than the face is not allowed.

Low dose topical cortisone therapy defined as  $\leq 30$  grams/week of an intermediate potency (class IV) topical steroid (or equivalent) is allowed, but the treated area must not exceed 10% of total body surface.

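### Non-inferiority is decided on the per-protocol set alone, so it would be declared even if the same test failed in the full analysis set

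*Protocol*

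**What the plan says.** The primary objective (section 2) is the ELISA response "in subjects with diagnosed atopic dermatitis compared to healthy subjects". Section 3.1 states: "This study is an open-label, controlled, phase II clinical trial". Group membership follows from disease status, not from randomisation.

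Section 9.3 defines the PP set as follows: "This is the subset of subjects who adhere to all protocol conditions, however, not relevant protocol violators can be included into this dataset". Whether a deviation counts as relevant "should be made case-by case in a blind review meeting". The protocol lists no criteria for relevance. The FAS is broader: "This is the subset of subjects who had received at least one dose of study vaccine and for whom any data are available". On the roles of the two sets, the text after naming PP as primary reads: "All confirmatory testing is based on this population. For further descriptive purposes, the same statistical procedures will be applied to the FA dataset".

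Among the conditions a subject could breach are the limits on topical treatment in section 6.6. The calcineurin inhibitor rule there is addressed to subjects with active AD and ends: "The use of calcineurin inhibitors on body areas other than the face is not allowed". The topical steroid limit that follows is not restricted to either group. Section 5.4 also lists a clinical need for disallowed therapy as a possible reason for withdrawal.

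**The concern.** A PP analysis is a usual choice for non-inferiority. The weakness is that it decides alone. The FAS test is run but cannot change the conclusion, and no rule covers disagreement between the sets.

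This arrangement deserves attention because deviations are unlikely to be balanced. A healthy subject has little reason to use topical calcineurin inhibitors or large amounts of topical steroid. A Group 2 subject with a flare may. Such a subject can have both doses and a Visit 4 titre, yet be left out of the confirmatory test if the review judges the deviation relevant, with little counterpart in Group 1. In an open-label trial an AD-medication deviation also reveals the group, so the review can be blind only to titres, and the protocol does not say that it is.

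Section 1.5 gives possible immune defects in AD as the reason for testing the response. If the subjects left out respond less well, p2 - p1 is overstated in the direction that supports the claim.

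**Working it through.** **Inputs from the protocol.** Margin 5 points; 99% seroconversion in both groups; exact unconditional test with a one-sided 97.5% interval; 124 per group, 130 with drop-out (section 9.1 and synopsis); 230 healthy and 330 AD subjects in the complete population (Appendix V). I read the decision limit as -5%, as the hypotheses in 9.1 require, and use one-sided 0.025 to match the interval.

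**The plan's own figure.** Full enumeration of the exact unconditional test at 99% versus 99% gives, with score ordering, 73.9% power at 124 per group and 81.8% at 125. With unpooled-Z ordering it gives 80.7% at 124. The stated 124 is therefore reproduced to within one subject per group. Drop-out: 124 / 0.95 = 130.5, against 130 stated.

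**How few failures decide the test (score ordering, one-sided 0.025).** Largest number of AD failures that still passes:

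- 124/124: 1, 1, 2 for 0, 1, 2 healthy failures
- 130/130: 1, 2, 2
- 230/330: 8, 9, 10

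**Assumptions for size.** The protocol gives neither the share f of AD subjects excluded from PP nor their seroconversion rate r. I take f = 5% and 10%, and r from 94.2% (the one-dose Day 28 figure in Table II, 49/52) down to 70%. Only AD subjects are excluded, and everyone else seroconverts at 99%. At 330 AD subjects, f = 5% leaves 314 in PP (16 excluded) and f = 10% leaves 297 (33 excluded).

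**Overstatement of the AD rate** = f x (99% - r). For example, 5% x (99 - 80) = 0.95 points and 10% x (99 - 70) = 2.9 points.

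**Chance that PP passes and FAS fails.** Sum the binomial probabilities of healthy failures, retained AD failures and excluded AD failures over all outcomes where the test rejects at 230 versus the PP number but not at 230/330:

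| r in excluded | f = 5%: overstatement | f = 5%: PP passes, FAS fails | f = 10%: overstatement | f = 10%: PP passes, FAS fails |
|---|---|---|---|---|
| 94.2% | 0.24 pts | 0.35% | 0.48 pts | 1.35% |
| 90% | 0.45 | 1.1% | 0.90 | 5.7% |
| 80% | 0.95 | 5.7% | 1.90 | 34% |
| 70% | 1.45 | 16% | 2.90 | 72% |

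The pattern follows from expected FAS failures in AD. At f = 5%, r = 70%: 314 x 1% + 16 x 30% = 3.1 + 4.8 = 7.9, just inside the limit of 8 to 10. At f = 10%, r = 70%: 297 x 1% + 33 x 30% = 3.0 + 9.9 = 12.9, beyond it.

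**False claim at the margin.** Suppose the true rates are 99% healthy and 94% AD overall, at 230/330. With no exclusion, non-inferiority is claimed 2.0% of the time. With 5% excluded at r = 80%, the retained AD rate is (94 - 5% x 80) / 0.95 = 94.7% and the PP claim rate is 5.2%. With 10% excluded, the retained rate is (94 - 10% x 80) / 0.90 = 95.6% and the claim rate is 15%. If the excluded respond like the rest, it stays at 1.8% or below.

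**Power if both sets must pass.** With 99% in everyone and a random 5% of each group outside PP: at 130/130, PP alone 73%, FAS alone 81%, both 72%. At 230/330 all three are about 99.8% to 99.9%.

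**The case against.** PP as the primary set with the same test on the FAS is a conventional non-inferiority layout. Both results would be reported, so a discrepancy would be visible. Several stronger readings are tempting, and the protocol does not support them.

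- A reader might infer that a breach of 6.6 removes an AD subject from PP. It does not say so: violators whose deviation is judged not relevant stay in, and the criteria may be in the analysis plan.
- A reader might infer that excluded AD subjects are likely non-responders. Nothing links topical treatment to lower IgG. The specific deficits named in 1.5 concern cytotoxic T cells and interferon gamma, whereas the endpoint is an IgG ELISA. In Table II, seroconversion two weeks after the second dose was 100% at every dose level, in healthy subjects. The 94.2% used above is a one-dose figure, and the lower values of r have no source.
- The 5% is a drop-out allowance, and 9.3 counts as drop-outs those outside the FAS. It is not a PP exclusion rate. Table III offers a loose guide: 2 of 15 active-AD subjects had AD as an adverse reaction. With half of Group 2 active (the minimum in 4.1), that is 13.3% x 50% = 6.7%, but not every flare would breach 6.6.
- A reader might see a comparison of compliant AD subjects with all healthy subjects. Group 1 is restricted to PP as well.
- A reader might suspect the review because the sponsor's laboratory runs the ELISA. No section gives the reviewers access to titres, and 9.4.4 assigns data management and statistics to the contract research organisation.

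These limits stand, and so does the fact that entry rules (SCORAD at most 30, restricted topical treatment) already narrow the AD group. They do not supply the missing element: 9.3 itself makes the FAS result descriptive and leaves disagreement without consequence.

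**Conclusion.** The point holds in a limited form. As written, a PP pass is sufficient and an FAS failure has no effect on the claim. Because groups are disease-defined, the trial is open-label and the treatment limits bear mainly on Group 2, discretionary exclusion can be lopsided. That last step is a sound inference, not something the protocol states.

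The size depends wholly on assumed values of f and r. The effect is negligible if excluded AD subjects respond nearly as well as the rest, and becomes material only when the share excluded is near 10% and a fifth or more of them fail to seroconvert after vaccination. No bias has been shown, and PP as primary set is not an error in itself. This is a cheap improvement to the decision rule.

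**What to change.** In 9.3 and 9.4.2, declare non-inferiority only if the lower confidence limit exceeds -5% in both the PP set and the FAS. For this test, specify FAS subjects with a Visit 4 ELISA result, analysed regardless of protocol deviations. This must be spelled out because the FAS definition requires only one dose and any data, so some members may have no Visit 4 titre. In 9.3, also state that PP classification is completed before post-vaccination ELISA results are accessible to those deciding.

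The change is to wording. It needs no new data, and the FAS run is already planned apart from the Visit 4 specification. The power cost is about 1 point at 130/130 (73% to 72%) and almost nothing at 230/330, if subjects outside PP respond like the others. If they respond less well, the joint rule passes less often: at 230/330 with 5% of AD subjects excluded at 80% seroconversion, both sets pass about 94% of the time, against 99.8% for PP alone. That is the price of letting the full AD population count.
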